**Fig. 1 Fig1:**
[figure not shown]
Overview of the examination procedure

## Outcomes of the trial

### Primary outcome

#### Suicidal ideation

#### Beck scale for suicide ideation (BSS)

The primary outcome in the trial is the change in suicidal ideation severity from baseline measure (t_1_) to post assignment (t_2)_ and the follow-up assignments (t_3_ and t_4_). Suicidal Ideation is measured at each assessment by the *German Version of the Beck Scale for Suicide Ideation* (BSS [23];). The Beck Scale for Suicidal Ideation is a self-report instrument for assessing the patient’s severity of suicidal tendencies. For this purpose, 21 statements on a rating scale ranging from 0 to 2 are evaluated as self-assessments and the frequency and seriousness of previous suicide attempts are reported. BSS questions are related to the participant’s wish to live, wish to die, frequency of suicidal ideations, perceived capability to carry out an attempt, extent of actual preparation, and similarly oriented queries. The responses of 19 BSS items are summed up to create an index of suicidal ideation ranging from 0 to 38 with higher scores reflecting greater ideation. The German scale has been found to be a valid and reliable measure of suicidal ideation [24]. The English version of the BSS is widely used in suicide research and has demonstrated predictive validity for suicide attempts and deaths by suicide [25]. The BSS is administered at all study time points.

### Secondary outcomes

#### Depression

#### Beck depression inventory-II (BDI-II)

The BDI-II is a 21-items self-report inventory of depressive symptomatology used to measure depression [26]. It is one of the most widely used research instruments for this purpose and has demonstrated good psychometric properties for use with an inpatient population [27]. Each item is rated on a rating scale from 0 to 3, with higher scores indicating more severe levels of depressive symptoms. Previous studies have reported BDI-II means of 12.75 in a nonclinical student sample [28] and of 21.02 in an inpatient sample [29].

#### General symptom burden

#### Symptom Checklist-18-Mini (SCL-18-Mini)

The SCL-18-Mini is a self-report questionnaire that measures the current extent of the general symptom burden with 18 items [30]. On a Likert scale from 0 (not at all) to 4 (very much), patients should indicate how much they have suffered from various complaints in the last 7 days. Three subscales (somatisation, depression, anxiety) and an overall index for mental distress can be calculated. There are excellent coefficients for the internal consistency (Cronbach’s Alpha); results for convergent, discriminant, and differential validity are satisfactory to good [31].

#### Reasons for living

#### Brief reasons for living inventory (deutsche version) (B-RFL)

The B-RFL is a 12-items form of the *Reasons for Living Invent*ory which functions as a self-report inventory for patients to rate how important each item would be for living if a suicide is contemplated. Inventory Items are rated on Likert Scales of 1 (not at all important as a reason of not killing myself) to 4 (very important as a reason of not killing myself), with higher scores reflecting higher reasons to live [32, 33].

The assessment explores the importance of family and children, religious values, beliefs in the own capabilities, and the value of living in general. It also assesses the fears one may have about what others would think as well as the potential pain involved in a suicidal act which can be important considerations when someone contemplates suicide. The B-RFL has strong psychometric properties and has been shown to be comparable to the Beck Depression Inventory (BDI) or the Beck Hopelessness Scale (BHS) for predicting suicidality [34, 35]. The Brief Reasons for Living Inventory, which has not yet been published in German, was translated from English into German for our study. In order to check and guarantee the linguistic and content-related correctness, a translation-back-translation procedure was conducted with a native speaker.

#### Therapeutic relationship

#### German version of the scale to assess the therapeutic relationship in community mental health care, patient-version (D-STAR-P)

The quality of the therapeutic relationship will be assessed by the patient-version of the D-STAR. The D-STAR-P is a 12-items self-report questionnaire with three subscales: Positive Collaboration, Positive Clinician Input, and Nonsuppurative Clinician Input. Loos et al. (2011) found the psychometric properties to be acceptable [36]. The feasibility and internal consistency of the D-STAR-P was good and there is evidence of good convergent validity.

#### Suicidality

#### Suicide status form (SSF; CAMS condition only)

Administration of the *Suicide Status Form* (initial, interim/tracking, and outcome/disposition versions) is an integral part of the CAMS framework. The SSF is administered within a collaborative engagement process with the patient, as described in the CAMS treatment manual [13]. The SSF is a multifaceted instrument, which is used in the course of the CAMS approach for risk assessment, treatment planning, tracking of risk, as well as for documenting all clinical outcomes. The SSF Core Assessment is made up of five items asking for subjective ratings (0–5) various suicide-related states: psychological pain, stress, agitation, hopelessness, and self-hate (there is also a rating of overall behavioural risk). This set of variables is administered at the start of every CAMS session through the course of care and has strong psychometric validity and reliability with suicidal inpatients [37]. The first three variables (pain, stress, and agitation) are based on Shneidman’s cubic model of psychic pain that lies at the heart of his formulation of the suicidal experiences [38]. The SSF also obtains patient’s sense of hopelessness (based on the work of Aaron Beck), and self-hate which is based on Baumeister’s work conceptualizing suicide as an escape from the pain of self-loathing [39, 40]. The SSF is further divided into additional sections to assess the current risk of suicide and to plan treatment. Responses from the assessment sections of the SSF are used to inform the CAMS Stabilization Plan as well as CAMS treatment goals that focus on patient-defined drivers which make them consider suicide.

### Additional measures

In addition to the outcome measures described above, sociodemographic data (including age, gender, education and current living situation) are recorded for all examination times. Furthermore, a short documentation of medication will take place. This information is gathered in order to describe the characteristics of the study sample.

### Exploratory measures

In order to generate hypotheses for forthcoming studies and to improve our inpatient treatments, the following exploratory outcome is assessed:

#### Components of inpatient treatment

#### Questionnaire to assess the factors subjectively experienced as helpful in the context of inpatient crisis intervention

The questionnaire for the evaluation and assessment of the impact factors of crisis treatment was prepared by us for this study. Patients describe on 14 items how helpful they found different aspects of their inpatient treatment, such as therapeutic sessions, contact with other patients, pharmacotherapy, the setting of the clinic, the help of the social worker etc., and in terms of their overall stabilisation. Inventory items are rated on a Likert Scale from 1 (not helpful at all) to 6 (extremely helpful), with higher scores indicating more satisfaction with the treatment. In addition, patients are asked to assign a letter grade for inpatient treatment and asked to reflect on their health before and after treatment.

We have intentionally limited the number of research measures in order not to overtax patients but believe we will have sufficient data for a meaningful and thorough research endeavour. Completion of the baseline and the follow up questionnaires (t_1_, t_2_, t_3_, t_4_) will take patients approximately 20–30 min each. The test batteries are handed over by the responsible therapist and are administered by the research assistant, who is blind to the patient’s treatment condition.

### Study center

The treatments are provided at the Clinic of Psychiatry and Psychotherapy, Ev. Hospital Bethel in Bielefeld, Germany. The clinic is responsible for the hospital mental health care of the city of Bielefeld with over 340,000 inhabitants. The study is being carried out on a crisis ward with 22 treatment beds; approximately 600 inpatient admissions are performed annually with a mean duration of stay of 13 days (range 1 to 60).

### Study sample

#### Participant inclusion and exclusion criteria

Patients with acute suicidal thoughts or behaviours are included who fluently speak and read the German language and who are capable to agree to participate in the study and provide written informed consent. Most patients are expected to suffer from affective and/or anxiety disorders and/or personality disorders. This study is only treating suicidal inpatients. The consent, legal capacity, and cognitive capacities are clinically evaluated. When participation is clinically judged to be contraindicated for a particular patient, they are excluded from the study.

Patients are also excluded who are chronically suicidal and/or have been treated in an inpatient psychiatric setting for a total of more than 12 weeks within the last 12 months, or who have been admitted more than 6 times during this period, or who live in an assisted living facility. In addition, patients with a psychotic disorder during the last 12 months, an eating disorder with BMI < 16 and/or a current substance dependence are excluded. Substance abuse or previous substance dependence are not exclusion criteria. Patients who are currently suffering from psychotic symptoms as part of an underlying depressive disorder are also excluded, as are patients with developmental disabilities, dementia or an organic condition. Patients are also excluded, who, at the time of admission, have already planned further long-term inpatient or day-clinic treatment to continue after crisis intervention therapy without being discharged in the meantime, as well as those, who have to be treated on our crisis ward for longer than 40 days. However, the duration of the treatment must be at least 10 days in order to ensure that patients receive a sufficient extent of treatment (at least three sessions following the admission interview). The exclusion criteria are established at the time of admission (t_1_) and validated by using the diagnostic interview any few days later. Patients who are committed against their will as per civil legal requirements (PsychKG of the federal state of North Rhine-Westphalia or the nationwide valid law of care) do not take part in the study.

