### Trial design

In our pragmatic randomized controlled trial at the Clinic of Psychiatry and Psychotherapy, Ev. Hospital Bethel, Germany, CAMS is being compared to E-TAU within an inpatient crisis setting. The trial is designed as a single-center, two-armed, parallel-group, observer-blinded randomized clinical effectiveness trial. Since we assume that about 50% of the patients we initially examine do not meet the inclusion criteria, 20% do not consent to participate in the study and 20% discontinue treatment, we plan to examine 144 patients of the Clinic who are admitted to the ward due to acute suicidal risk (thoughts or behaviors) in order to obtain our target sample size of 60 patients. After screening and randomizing, the study participants will be followed for about 6 months at four checkpoints t_1_, t_2_, t_3,_ t_4_.

Individuals who are screened positive for the trial and who gave their written informed consent to take part in the study are asked to complete a set of questionnaires (t_1_) on the admission day or on the workday following the admission day. Then, the patient is randomized and informed about their group membership and the respective interventions begin on the following day. A second follow up assessment (t_2_) is carried out between 10 and 40 days later at the day before discharge. Another follow-up assessment will be arranged for 4 weeks after discharge (t_3_). Five months after the end of treatment, patients will receive the assessment instruments again by mail (t_4_). Refer to Fig. 1 for a schematic overview of the time flow of the trial and see Appendix 1 for the complete review of the study questionnaires.

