CAMS treatment follows a pre-defined format, using the SSF as a multipurpose assessment and treatment planning tool. The continuous monitoring and work on reducing the impact of patient-defined suicidal drivers also creates alternative solutions and perspectives over the course of the sessions ensuring high-quality suicide-focused treatment that also creates detailed medical record documentation. A typical treatment course in our study is characterized by employing two sessions weekly of 30–60 min duration. Every session is initiated by filling out the SSF in a side-by side manner. In the first session, approximately 20 min are used to fill out the first part of the SSF as part of the SSF Core Assessment. At the start of all interim CAMS sessions, approximately 5 minutes is used to complete the SSF Core Assessment (as a repeated measure across CAMS-guided care). A problem-focused treatment plan directly addressing the patient’s suicidal drivers is jointly developed during the first session and routinely evaluated and updated in each following CAMS session. Furthermore, as part of CAMS-guided care, a stabilization plan is developed during the first CAMS session and evaluated and improved during every consecutive session in order to increase the patient’s suicide-related coping skills. Thorough the course of CAMS-guided care stabilization and treating suicidal drivers are central to effective care. Thus, ongoing CAMS care consists of developing adequate coping skills and helping the patient identify and cope with their suicidal drivers more effectively. Within the CAMS framework, suicidal drivers are further divided in two categories; direct and indirect drivers. Direct drivers are thoughts, feelings, or behaviours that increase specific suicidal risk (e.g., being sexually abused as child or break up of a marriage). Indirect drivers are factors that do not produce acute suicidal states but instead increase the vulnerability and the potential activation of direct drivers (e.g., drinking, isolation, insomnia). The CAMS approach does not require any therapeutic orientation and does not prescribe precise interventions as to how exactly suicidal drivers should be treated, which means that the therapist rely on interventions that can treat driver problems (e.g., insight-oriented work, vocational counselling, couples therapy, exposure treatment for trauma).

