There are no mandatory homework assignments during a CAMS course of care. The duration of CAMS-guided care is dependent on the treatment progress and varies between patients. The treatment is concluded when the clinician and the patient agree that the acute danger of a suicidal act is eliminated, adaptive coping skills are developed while the patient scores him/herself below 3 on subjective suicidal risk rating (on a 5-point scale) and that they are managing any suicidal thoughts or feelings while remaining behaviorally stable which may trigger discharge from the inpatient setting. In the present RCT, cases who have received between 4 and 9 CAMS sessions including the initial session will be analysed. See Appendix 2 for the complete CAMS Material.

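### Treatment duration is written as an admission criterion but is known only after randomisation, so it can remove randomised patients, and the lower session limit is three in some sections and four in another

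*Protocol article*

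**What the plan says.** **Eligibility** (Participant inclusion and exclusion criteria). The article states that "the duration of the treatment must be at least 10 days in order to ensure that patients receive a sufficient extent of treatment" and explains the purpose as "at least three sessions following the admission interview". It excludes patients "who have to be treated on our crisis ward for longer than 40 days". On timing, it says "The exclusion criteria are established at the time of admission", with a check by diagnostic interview some days later.

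**Treatment.** Under Trial design, randomisation follows the baseline questionnaires and "the respective interventions begin on the following day". The CAMS section says "A typical treatment course in our study is characterized by employing two sessions weekly of 30–60 min duration". It makes the length of CAMS care depend on progress, and reaching its end point may lead to discharge. It then says "cases who have received between 4 and 9 CAMS sessions including the initial session will be analysed". The E-TAU section gives three to nine sessions during treatment at roughly two a week, plus one afterwards. Treatment feasibility defines a dropout as someone who stops before completing three sessions.

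**Removal and analysis.** The withdrawal section lets investigators take a participant out of the trial if an exclusion criterion comes to light after inclusion. The sample-size section randomises 72 to obtain 60 in what it calls the intention-to-treat sample. Its 20% loss covers patients who discontinue and patients excluded because of further inpatient treatment. Statistical analyses promises to analyse all participants as randomised, including those who discontinue treatment.

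**The concern.** A rule fixed at admission can only use what is known at admission. Actual treatment duration is not known then. It unfolds after allocation, in a trial where patients and therapists are unblinded and where the same therapists treat both arms. If CAMS changes how quickly patients become ready for discharge, duration and session count are partly effects of treatment.

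The wording gives a route by which such a variable could decide who is counted. A patient who improves and leaves before day 10 fails the duration rule as written, and so does one kept beyond day 40. Either could be treated as having an exclusion criterion found after inclusion. Separately, a CAMS patient with fewer than four sessions falls outside the range the CAMS section says will be analysed. Losing fast improvers would work against an arm and losing slow ones would favour it, so the direction of any bias cannot be foreseen. In a trial of 60, a few such removals that differ between arms would undermine the protection randomisation gives.

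The session limits add a second problem. Four is the minimum for analysed CAMS cases, while three is the minimum elsewhere, so the same exposure can be adequate in one arm and not in the other.

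**Working it through.** **1. The plan's own figure: three sessions from 10 days.** Inputs are 10 days (eligibility section) and two sessions a week (CAMS section; E-TAU says approximately two).
- By rate: 2 × 10/7 = 2.86, about three.
- Counting from the first treatment day with alternating gaps of three and four days, sessions fall on days 1, 4, 8 and 11 (or 1, 5, 8 and 12). Ten days hold three sessions, and the fourth comes on day 11 or 12.
- Counting instead from admission, with 1 to 3 days before treatment starts: 2 × 9/7 = 2.57 down to 2 × 7/7 = 2.0.

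So 10 days roughly matches three sessions, though it does not ensure them if the days run from admission. It reaches four on neither count.

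**2. Calendar check (scheduling assumptions mine).** Seven admission weekdays; baseline on the admission day or next workday; treatment from the following day; sessions on Monday/Thursday or Tuesday/Friday; last usable day the day of discharge or the day before. This gives 7 × 2 × 2 × 2 = 56 equally weighted cases per stay, with days counted from admission.

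| Stay (days) | At least 3 sessions | At least 4 sessions |
|---|---|---|
| 10 | 45% | 0% |
| 12 | 89% | 11% |
| 13 | 98% | 30% |
| 14 | 100% | 57% |
| 16 | 100% | 93% |

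**3. Lower session limits side by side.**
- Eligibility: three, after the admission interview.
- E-TAU: three during treatment, plus one afterwards.
- Dropout: fewer than three.
- CAMS cases to be analysed: four, including the initial session.

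A CAMS patient treated for 10 days with three sessions therefore meets the duration rule, is not a dropout, and lies outside the analysed CAMS range. An E-TAU patient with the same exposure meets every stated limit.

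**4. Upper end.** 2 × 40/7 = 11.4 sessions, or 10.6 to 11.1 after a lag of 3 to 1 days, against a limit of nine. In the calendar check, 2% of cases exceed nine at 32 days, 57% at 35 days and 100% at 40 days. This holds only if the rate continues unchanged to the end of the stay.

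**5. Patient flow.** 144 × 0.5 = 72 randomised. The plan targets 60, so 72 − 60 = 12 patients (12/72 = 16.7%) are outside the sample it calls intention to treat. The stated 20% loss would leave 72 × 0.8 = 57.6. An intention-to-treat sample under the article's own definition would contain all 72.

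**6. Order of events.** Baseline, randomisation, treatment, progress, end of treatment. Actual duration and session count both arise after allocation. The withdrawal rule and the CAMS analysis range act on them; the statistical section says they should not matter.

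**The case against.** **The duration rule can be read as a forecast.** Patients who have to stay beyond 40 days are most naturally those expected to at admission. That is fair for the upper limit. The lower limit is worded as a requirement on the treatment itself, without any reference to expectation, and the withdrawal rule gives a way to enforce it later.

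**Intention to treat is already promised.** It is, and the article also plans to keep assessing patients who discontinue. So the documents do not show that anyone will be removed for duration. They contain rules that permit it alongside a statement that forbids it, and they do not say which prevails. Because these are stated rules in conflict, this is not detail left to a fuller document.

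**Three and four may be the same count.** If the admission interview were the initial session, 1 + 3 = 4. But that interview precedes randomisation, and the first CAMS session is described as the one where the status form is first completed and the treatment and stabilisation plans are made. If the post-treatment session counts, 3 + 1 = 4, but the E-TAU upper limit then becomes 9 + 1 = 10 against nine for CAMS. Neither reading is stated.

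**The upper-end mismatch is extrapolation.** This largely stands. The rate is described as typical or approximate, and nine can be read as a cap.

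**Stronger readings.** A reader might infer that the typical patient on this ward, with a mean stay of 13 days, meets one rule and fails the other. The documents do not support that: the mean covers all admissions, not trial patients, and the article gives no distribution. Under four assumed distributions with mean 13 (exponential, gamma with shape 2, lognormal with coefficient of variation 0.6 and 1), 29% to 42% of stays within 10 to 40 days last 10 to 14 days and 2% to 5% exceed 35 days. That leaves 56% to 66% in between, where both rules are usually met. A reader might also infer that the trial excludes the patients its rationale is about. It does not follow: the abstract itself pairs short treatment with 10 to 40 days.

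**Conclusion.** The concern holds in two parts.

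First, the article treats actual duration as an admission criterion although it is known only after allocation and, under CAMS, depends on progress. With the withdrawal rule, the reduction from 72 to 60 and the CAMS session range, this permits exclusion on a post-randomisation variable, against the commitment to analyse everyone as randomised. The 12 of 72 patients (16.7%) outside the target sample are an allowance for all losses, not a count of removals for duration. That count, and the size and direction of any bias, cannot be derived from the article.

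Second, the lower session limit is three in the eligibility, E-TAU and dropout text and four for analysed CAMS cases. At about two sessions a week, 10 days gives about three, so a patient can satisfy the first set and fall outside the second. This rests on the stated approximate rate. The percentages in the calendar table also rest on the scheduling assumptions, but the inconsistency between the limits does not.

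The upper-end mismatch is possible but unproven. The point is worth correcting because the conflict affects who enters the comparison and the remedy is cheap.

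**What to change.** 1. Word the criterion as expected treatment duration, judged and recorded before the allocation is made.
2. State that actual duration and number of sessions change neither eligibility nor inclusion in the primary intention-to-treat analysis. If an analysis by CAMS session count is kept, label it as secondary.
3. Recruitment opened in March 2017 and was expected to finish in autumn 2019, so a new screening field cannot help patients already enrolled. For them, analyse everyone as randomised and report, by arm, anyone removed because of duration or session count.
4. Reconcile the duration window, session frequency, session ranges in each arm, dropout definition and analysis set across the eligibility, CAMS, E-TAU, feasibility and statistical sections. Say whether the admission interview and the post-treatment session count. Which values apply is for the clinical team.

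The cost is protocol wording, one field on the screening form and a short table in the report. The downside is that some analysed patients will have had little exposure, which slightly dilutes the contrast between arms.
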